## Abstract

**Introduction:**

Cerebral palsy (CP) can now be diagnosed in infants with identified CP risk factors as early as three months of age; however, many barriers prevent equitable access to early detection pathways. The “Partnering Early to Provide for Infants At Risk of Cerebral Palsy” feasibility study (PĒPI ARC) seeks to trial a new approach to decrease inequitable health service in Aotearoa New Zealand for high-risk infants and their families. PĒPI ARC incorporates face-to-face clinics, an in-person and virtual Hub, and the use of telehealth to enable flexible access to CP assessments and support for health professionals in early CP detection.

**Methods and analysis:**

A non-randomised feasibility study was conducted from a tertiary Neonatal Intensive Care Unit (NICU) in Wellington and included seven regional referral centres, servicing nearly 30% of the total population in New Zealand (NZ). The families of infants with a high risk of neurodevelopmental impairment and health professionals interacting with the Hub were invited to participate. Mixed methods were used to evaluate the (i) equitable implementation of an early detection pathway, (ii) acceptability, (iii) demand among families and health professionals, (iv) efficacy in relation to reducing the age of receipt of CP diagnosis, and (v) the experiences around communication and information sharing.

**Ethics and dissemination:**

The NZ Health and Disability Ethics Committee approved this study (HDEC: 2022 FULL 13434). The findings will be disseminated in peer-reviewed journals, in conference presentations, and via professional networks.

**Clinical trial registration:**

Australian New Zealand Clinical Trials Registry: ACTRN12623000600640.

## Introduction

In Aotearoa New Zealand (NZ), it is estimated that every 3 days a baby is born who will later receive a diagnosis of Hōkai Nukurangi, the Te Reo Māori term for cerebral palsy (CP) (1). Of these babies, approximately 60% are diagnosed after 12 months of age, with a reported median age of CP diagnosis at 17 months of age in NZ (1). Many families of children with CP living in NZ perceive diagnosis delays, with nearly 20% of them reporting delays of more than 12 months (2).

Historically, CP has been diagnosed using a combination of clinical and neurological signs, which often do not appear until the child is older. In 2017, an international evidenced-based guideline was published for accurate and early CP diagnosis using a combination of different assessment tools (3). Through a combination of brain Magnetic Resonance Imaging (MRI), the Prechtl General Movements Assessment (GMA) (4), and the Hammersmith Infant Neurological Examination (HINE) (5), infants with detectable newborn risk factors for CP can now be diagnosed as early as 3 months of age (corrected for prematurity) with a sensitivity and specificity of 97% and 99%, respectively, in a retrospective case–control study (6). The successful implementation of these recommendations has seen significant reductions in the age of identifying “high risk of CP” [e.g., in an Australian clinic with an average age of 4.4 months (7)] and the average age of CP diagnosis [e.g., in a US clinic from 18 months prior to implementation down to 12 months (8), in a network of US clinics 19.5 months to 9.5 months (9), and in an Australian clinic to 8.5 months (7)].

Based on international recommendations (3, 10), the NZ Cerebral Palsy Clinical Network (CPCN) in 2020 developed the national *Best Practice Recommendations for Early Detection of CP, Intervention, and Monitoring* (CPCN Recommendations) to support the implementation of early clinical CP detection pathways across NZ. The development of the CPCN Recommendations addresses the need to provide clear pathways (11) and guidance for consistent assessment approaches (12), but it does not remove other barriers to implementing early detection in practice. These barriers, as reported by health professionals, include the lack of resources and multidisciplinary teams (12); poor coordination between hospital, community, and regional follow-up; and inequitable access to services (11–13). Families report dissatisfaction and distrust with the diagnostic process, delays in diagnosis, and issues with communication and access to practical and emotional support (2). In response to these concerns, co-design workshops for Māori and non-Māori families were conducted and revealed the need for improved service provision and navigation within a complex health system, with a “one-stop shop” solution proposed as a more equitable and culturally safe system (14). The “Partnering Early to Provide for Infants At Risk of Cerebral Palsy” (PĒPI ARC) Hub seeks to incorporate these learnings within the implementation of the CPCN Recommendations.

### PĒPI ARC

The PĒPI ARC Hub applies a modified multidisciplinary team (MDT) approach to health service delivery and care for infants with detectable risk factors for CP who are admitted to a tertiary neonatal intensive care unit (NICU). The Hub aims to develop a Māori-centered relationship model of care with Whanaungatanga (connectedness) and Whakawhanaungatanga (building relationships) at its core (15), incorporating the key interrelated dimensions of Māori holistic healthcare including wairua (spiritual), whānau (extended family network), hinengaro (the mind, emotion), and tinana (physical). Whānau represents the collective way Māori operate. People do not exist in isolation but include a person's immediate and extended family. PĒPI ARC embraces the view that at the centre of care is the patient (i.e., infant) and their extended family and seeks to (1) build relationships and connections through the journey of infants in NICU, their transition to home, and follow-up support in their community (16) and (2) to coordinate care and minimise the burden for families in attending multiple appointments with different health professionals.

The Hub provides three functions:
1.A face-to-face clinic for infants and their families living in Wellington2.Support to families and infants who reside in other regions to access GMA and HINE assessments, by working in close partnership with the families, their local doctors, and therapists3.Partnership with, and support for, local and regional health professionals to use early detection strategies and communication with families

### Study aim, objectives, and hypotheses

This study aims to evaluate the feasibility of equitable implementation of a pathway for the early detection of CP for infants with newborn detectable risks (criteria outlined in Table 1) who are admitted to a tertiary NICU in NZ through a multidisciplinary regional Hub called the PĒPI ARC Hub. Based on the work of Bowen et al. (17), (i) **implementation**, (ii) **acceptability (**18), (iii) **demand,** and (iv) **limited efficacy** of PĒPI ARC will be studied.

**Table 1 T1:** Criteria for infants within the newborn detectable risks, as outlined in the New Zealand CPCN best practice recommendations for early detection of cerebral palsy (CP), intervention, and monitoring (CPCN recommendations).

Newborn detectable risk criteria
1. Any infant born <28 + 0 weeks gestation. OR 2. Any infant born ≥28 + 0 weeks gestation with one or more detectable risk factors for CP: i. Weight < 1,000 g ii. Intrauterine growth restriction Birth weight <3rd percentile on population-based or customised growth charts or at clinician's discretion based on concern about pathological growth restriction. iii. Abnormal findings on neuroimaging associated with CP [e.g., Grade 3 and 4 intraventricular haemorrhage, post-haemorrhagic ventricular dilatation, hydrocephalus, periventricular leukomalacia (PVL), stroke, brain maldevelopment]. iv. Hypoxic ischaemic encephalopathy (HIE)—Grade 2 and 3. v. Neonatal encephalopathy of other aetiology. vi. Neonatal meningitis/ encephalitis—bacterial or viral. vii. Cardiac surgery viii. Clinical or parental concerns or other significant risk factors—clinician discretion.

### Primary objective

1.**Implementation:** to determine to what extent the CPCN Recommendations for early CP diagnosis can be equitably implemented for infants with newborn detectable risks who are admitted to a level 3 NICU (independent of place of residence and ethnicity) and if the fidelity of the CPCN Recommendations can be maintained

### Secondary objectives

2.**Acceptability:** to evaluate the acceptability of a PĒPI ARC Hub model of care by families and health professionals3.**Demand:** to determine the demand for the PĒPI ARC Hub among both local and regional families and health professionals4.**Limited efficacy**:
i.To evaluate if the PĒPI ARC Hub model reduces the age of diagnosis of CPii.To explore the experiences around communication and information sharing between families and health professionals

### Hypotheses

**H1**: Equivalent levels of infants who meet the criteria will undergo assessments with CP-specific diagnostic tools outlined in the CPCN Recommendations, independent of region of residence or ethnicity.

**H2**: Whānau and health professionals will find the PĒPI ARC Hub model of care acceptable (over the acceptability constructs).

**H3**: The demand will be high with infants who meet the criteria choosing to enroll in the PĒPI ARC study over standard care.

**H4**: More than 34% of infants with CP will be diagnosed before 12 months of corrected gestation age (CGA) and >17% before the age of 6 months CGA.

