### Study design and setting

The PĒPI ARC study is a prospective, non-randomised, feasibility study that uses a mixed methods approach to evaluate the previously outlined domains of feasibility. The study will run from March 2023 to September 2024, with the primary time point being at the completion of the PĒPI ARC Hub trial period. The study setting will be a regional Hub based in Wellington to allow follow-up of eligible infants who received care at the Wellington NICU. The PĒPI ARC Hub will be delivered using two components: a community-based, multidisciplinary face-to-face diagnostic clinic in Wellington and a virtual Hub to support regional CP-specific neurodevelopmental follow-up, education, and information sharing and foster relationships among the Wellington team, local community, and regional child development services (CDS) and paediatricians.

The Wellington NICU is a tertiary unit that provides perinatal and surgical care for infants from Wellington and seven regional referral centres from half of the North Island and the top of the South Island of NZ. The unit cares for a third of all infants admitted to a tertiary NICU in NZ. It is estimated that between 100 and 120 infants per year will fit the criteria for the CPCN Recommendations pathway, of which approximately 30% live in the Wellington area (21) (i.e., to be invited to attend the in-person clinic), and the remainder will receive follow-up in their local regions (supported by the PĒPI ARC team through telehealth).

For the Wellington NICU catchment area, data from the NZ CP Register (2009–2020) showed that 17% of infants received a diagnosis of CP before 6 months of age and 34% before 12 months (22).

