### Participants and recruitment

Participants for this study will be formed by two groups, namely, the infants and their parent/caregivers, and the health professionals involved/interacting with the PĒPI ARC Hub. There are no limits placed on the sample size, and a formal sample size calculation is not required. Based on the historical figures of the number of infants admitted to the NICU at the Wellington Regional Hospital and infants aged <28 weeks, up to 120 infants are anticipated to meet the study eligibility during the 12-month recruitment period. There will be no restrictions on other care or interventions partaken in by participants.

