MRI, Magnetic Resonance Imaging; GMA, General Movements Assessment; HINE, Hammersmith Infant Neurological Examination; CP, cerebral palsy; CGA, corrected gestational age; ICFQ, The Feeding Matters Infant and Child Feeding Questionnaire.

^a^
Scored by the GMA team or at least two senior assessors (inter-rater reliability of the assessors will be established beyond 80% prior to PĒPI ARC clinic appointments beginning). If consensus on scoring is not reached, the GMA will be reviewed independently by a third assessor, including referral to expert assessors if needed until consensus is reached.

**Table 3 T3:** Process plan for communicating outcomes to families/health professionals.

If an infant is assessed to be at low risk of CP: • Verbal and written feedback will be provided to the family and local team. • The infant will be discharged from the PĒPI ARC clinic to usual care.
If the assessments are inconclusive: • Explanation of inconclusive findings will be provided verbally and documented in clinic letters provided to the family and neonatologist/therapist. • The infant will be seen in the PĒPI ARC clinic for further assessment in 2–4 weeks for a repeat clinical examination.
If an infant is diagnosed with CP or high-risk of CP: • The family will be offered a follow-up appointment with the PĒPI ARC team including the social worker within 1–2 weeks’ time (face to face or telehealth based on their preference) to answer any questions and receive more information. All ongoing care will be with their local neonatologist/paediatrician and therapist. • Screening for comorbidities will occur, and genetic testing will be offered. Support and follow-up referral will be made. • Information about the diagnosis of high-risk of CP or CP, the referrals made, and advice about ongoing follow-up and monitoring will be provided to the family of the infant, primary neonatologist/paediatrician, therapist, and GP.

CP, cerebral palsy; GP, general practitioner.

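### H4 compares diagnoses captured only to September 2024 with register shares that include late diagnoses, so it is strongly biased towards confirmation

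*Protocol article*

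**What the plan says.** Under Hypotheses, H4 states "More than 34% of infants with CP will be diagnosed before 12 months of corrected gestation age (CGA"). For the earlier age it sets a second threshold: ">17% before the age of 6 months CGA". The denominator is infants with CP, not all enrolled infants.

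The thresholds come from Study design and setting, where register data for 2009–2020 in the Wellington NICU catchment "showed that 17% of infants received a diagnosis of CP before 6 months of age and 34% before 12 months". For the country as a whole, the Introduction reports that "approximately 60% are diagnosed after 12 months of age, with a reported median age of CP diagnosis at 17 months of age in NZ".

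On timing, Study design and setting says "The study will run from March 2023 to September 2024, with the primary time point being at the completion" of the Hub trial period. Outcome measures and data collection gives the same March 2023 to September 2024 window for every outcome in Table 4, including age at diagnosis. Participants and recruitment says "up to 120 infants are anticipated to meet the study eligibility during the 12-month recruitment period", and infants are recruited during the NICU stay. The article gives no later age at which CP status is established and no follow-up after September 2024. The Discussion confirms that there is no control group.

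**The concern.** The benchmark and the study proportion share a name but not a denominator. The register covers many birth years and includes children diagnosed late. In the study, a child counts as having CP only if diagnosed by September 2024. An infant who is 8 months corrected age on that date is either a case diagnosed before 12 months or not yet a case. That infant cannot appear as a late diagnosis.

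H4 is the only numerical hypothesis attached to the objective of reducing the age at CP diagnosis. Read as written, a Hub that changed nothing would probably be reported as having brought diagnosis forward. The average age at confirmed CP diagnosis in Table 4 is pulled downwards by the same mechanism.

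**Working it through.** **Inputs from the article.** Shares of CP diagnosed: 17% before 6 months and 34% before 12 months (register, catchment); national median 17 months. Recruitment of 12 months, during NICU admission; window March 2023 to September 2024.

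**Assumptions.** Recruitment starts in March 2023; accrual is uniform; the prematurity correction is 0–4 months; the register figures describe this cohort when the Hub has no effect. The cumulative diagnosis-age curve F is linear through F(0) = 0, F(6) = 0.17, F(12) = 0.34, F(17) = 0.50. Beyond 17 months it rises to 0.85 at 30 months, which matters little: a straight line from 17 months to 100% at 60 months moves the 83% below to no more than 84%.

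**Step 1: the plan's own figures.** With complete follow-up the shares are F(12)/1 = 34% and F(6)/1 = 17%, the H4 thresholds.

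**Step 2: age at cut-off, C.** September 2024 is 18 months (start of month) to 19 months (end of month) after March 2023. C is therefore uniform on 6–18 or 7–19 months before correction, and on 2–14 months at the low end (18-month window, 4-month correction).

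**Step 3: expected shares with no effect.** A case is known only if diagnosed by age C, so

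- share before 12 months = E[F(min(C,12))] / E[F(C)]
- share before 6 months = E[F(min(C,6))] / E[F(C)]

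For C on 7–19:

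- E[F(min(C,12))] = (5/12) × 0.2692 + (7/12) × 0.34 = 0.3105, where 0.2692 is the mean of F over 7–12 months.
- E[F(C)] = (5/12) × 0.2692 + (5/12) × 0.42 + (2/12) × 0.527 = 0.375.
- Shares: 0.3105/0.375 = 83%, and 0.17/0.375 = 45%.

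For C on 2–14:

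- E[F(min(C,12))] = (10/12) × 0.1983 + (2/12) × 0.34 = 0.2219.
- E[F(C)] = (10/12) × 0.1983 + (2/12) × 0.372 = 0.2273.
- E[F(min(C,6))] = (4/12) × 0.1133 + (8/12) × 0.17 = 0.1511.
- Shares: 0.2219/0.2273 = 98%, and 0.1511/0.2273 = 66%.

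| Age at cut-off (months) | At or past 12 months | Eventual cases known | Share <12 m (threshold 34%) | Share <6 m (threshold 17%) |
|---|---|---|---|---|
| 7–19 | 58% | 38% | 83% | 45% |
| 6–18 | 50% | 35% | 86% | 49% |
| 4–16 | 33% | 29% | 93% | 58% |
| 3–15 | 25% | 26% | 95% | 62% |
| 2–14 | 17% | 23% | 98% | 66% |

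**Step 4: least favourable curve.** Suppose every child not diagnosed by 12 months is diagnosed just after. For C on 7–19, E[F(C)] = (5/12) × 0.2692 + 7/12 = 0.6955, giving 0.3105/0.6955 = 45% and 0.17/0.6955 = 24%. The other rows give higher shares.

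**Step 5: direction without the assumptions on accrual and curve shape.** For C up to 12, F(min(C,12))/F(C) = 1. For C above 12 it is 0.34/F(C), which is at least 0.34 because F(C) cannot exceed 1. The no-effect share therefore cannot fall below 34%, and it exceeds 34% whenever ascertainment is incomplete. The same reasoning holds for 6 months and 17%.

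**Step 6: small numbers.** The article does not state the number of CP cases, so 6 to 24 eventual cases were tried. Simulation used the 18-month window with a correction of 0 or 3 months, given at least one diagnosed case. The chance of beating both thresholds with no effect is 72–78% with 6 eventual cases, 88–90% with 12, 93–95% with 18 and 96–98% with 24. With complete follow-up, the binomial chance of exceeding 34% with no effect would be 33–43%, and of exceeding 17% would be 27–39%, over the same range of cases.

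**The case against.** The best defence is that H4 serves a secondary objective labelled limited efficacy, in an uncontrolled feasibility study whose outcomes for this objective are described rather than tested. That is true, and the primary objective is untouched. But H4 still sets numerical thresholds, and the benchmark and data window that make them incomparable are all stated in the article.

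Four stronger readings are tempting, and the documents do not support them.

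- *H4 is certain to be met.* The excess holds in expectation. With about 6 eventual CP cases, the chance of beating both thresholds is roughly three in four.
- *Most infants close before a late diagnosis is possible.* Without a prematurity correction, 50–58% reach 12 months by the cut-off. The statement holds only with a sizeable correction, and the gestation mix is not given. Recruitment at any point in the NICU stay also means that some preterm infants are older at cut-off than enrolment at birth would imply.
- *Late diagnoses are lost because low-risk infants leave the clinic.* Table 3 does say "The infant will be discharged from the PĒPI ARC clinic to usual care", but about 30% of eligible infants live in the Wellington area and are invited to that clinic. Clinic/medical data also describes collection from medical records and from local and regional professionals. No differential loss is shown.
- *All of the Table 4 age measure is equally biased.* It includes age at a preliminary high-risk finding, which the clinic assesses at about 12–16 weeks corrected age. Nearly all infants pass that age before the cut-off, so truncation there is much smaller.

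The curve also joins catchment shares to a national median, although the national share before 12 months is about 40% rather than 34%. This affects the size of the bias but not its direction (step 5).

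**Conclusion.** The concern holds as a strong bias towards confirming H4. With no Hub effect, the expected shares at the September 2024 cut-off are about 83–98% before 12 months against a threshold of 34%, and 45–66% before 6 months against 17%. Under the least favourable curve they are still at least about 45% and 24%. The sizes rest on the March 2023 start, uniform accrual, the 0–4 month correction and the interpolated curve. A recruitment start later than March 2023 would make the bias worse. The direction needs only that the register shares describe the no-effect case and that some late diagnoses fall outside the window. Exceeding the thresholds is highly probable, not certain, because the number of CP cases is unknown and may be small. Mean age at confirmed CP diagnosis is biased downwards too; the high-risk component much less so.

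**What to change.** Do not judge H4 by comparing the September 2024 proportions with 17% and 34%. Choose one of two routes:

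1. Recompute the register benchmark under the same truncated follow-up: give register children the study's distribution of age at cut-off, count only diagnoses made by then, and compare with those shares.
2. Declare H4 descriptive at study close, with no threshold claim.

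If later record follow-up or register linkage proves possible (the article describes neither for enrolled infants), assess H4 once all infants have reached a common later age, with the benchmark cut at that age.

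Whichever route is taken, report the number of CP cases and exact 95% confidence intervals, since passing a point threshold is weak evidence even with complete follow-up. Report age at the high-risk finding separately from age at confirmed CP. Cumulative incidence among all enrolled infants may be added as description, but its denominator is not infants with CP, so it does not test H4. State as a remaining limitation that the register population differs from a high-risk NICU cohort.

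The cost is a little analysis work and a less favourable H4 claim. Later follow-up or linkage, if pursued, would also need an ethics and registry amendment and a later readout.

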2. To evaluate if the fidelity of the CPCN recommendations can be maintained, including diagnostic assessments completed, communication with families, and related referrals	• Infant medical records/PĒPI ARC clinic notes • Records for assessments • Referral data • Questionnaire—health professionals • Semi-structured interviews with health professionals and families	The total number and proportion of diagnostic tests completed/not completed (i.e., not grouped by region or ethnicity). Of participants with a high risk of CP/CP detected: • The number of participants whose parents were informed of the diagnosis, and the age and acceptability of communication • The timing of therapist review post high-risk CP diagnosis • The timing of referral for surveillance of comorbidities and medical complications as indicated • The number of families receiving information about practical and emotional support
Acceptability		
3. To evaluate the acceptability of the PĒPI ARC Hub model of care by families and health professionals	• Questionnaires—families, health professionals, and the PĒPI ARC team. • Semi-structured interviews with families and health professionals	Data will be interpreted according to those families and health professionals involved in the Hub who were from Wellington compared with other regional centres
Demand		
4. To determine the demand for the PĒPI ARC Hub among families and health professionals	• PĒPI ARC clinic notes/statistics • Infant medical records (virtual Hub) • Communications with the PĒPI ARC team: logged as part of an audit trail. The full audit trail will be reviewed at the end of the study in combination with questionnaire data	Using the number of infants and families approached to take part in PĒPI ARC: • The proportion of families who consent to the study • The proportion of infants who attend the clinic • The proportion of infants who complete regional follow-up appointments with paediatricians/therapists • The proportion of families that chose to use telehealth • The number and profiles of health professionals accessing the Hub for support • The type of support requested by families and health professionals
Limited efficacy		
5. To evaluate if the PĒPI ARC Hub model reduces the age of CP diagnosis	• PĒPI ARC clinic notes • Infant medical records	• The average age when a preliminary high-risk CP or CP diagnosis was made and age (/rate) of CP confirmation

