#### Clinic/medical data

Quantitative data will be collected from medical records and PĒPI ARC clinic notes and through communication with local and regional health professionals. Data will include demographic and ethnicity information, indication for entry into the CPCN Recommendations pathway, and completion of assessments including timing and results, diagnostic outcomes, and referrals for monitoring and interventions.

Descriptive statistics will be used to report participant characteristics, recruitment rates, attendance rate in clinics, completion of diagnostic tools, referral for early intervention, and surveillance (Objectives 1, 2, 4, and 5, Table 4). Analysis of Likert scale data from family, health professional, and PĒPI ARC team questionnaires will also be analysed using descriptive statistics (Objective 3, Table 4). If data are determined to be normally distributed, then continuous data results will be reported using means and standard deviations, or if data are not normally distributed, then median and interquartile ranges will be reported (lower and upper quartiles). Pearson's chi-squared or Fisher's exact test will be used to compare the extent of implementation of the best practice guidelines between regions and ethnicities. A *p* value of <0.05 will be considered statistically significant.

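### H4's cut-offs equal the historical register rates, with no margin, interval or test, so exceeding them is not evidence that the Hub lowers age at CP diagnosis

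*Protocol article*

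**What the plan says.** The Hypotheses section gives H4 as two percentages among infants with CP: "More than 34% of infants with CP will be diagnosed before 12 months of corrected gestation age (CGA) and >17% before the age" (the second age being 6 months CGA). The source of the figures is in Study design and setting, where the NZ CP Register for the Wellington NICU catchment (2009–2020) "showed that 17% of infants received a diagnosis of CP before 6 months of age and 34% before 12 months".

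H4 belongs to secondary objective 4i, under limited efficacy, which asks whether the Hub model reduces the age of CP diagnosis. Table 4 lists this as Objective 5, with the measure "The average age when a preliminary high-risk CP or CP diagnosis was made and age (/rate) of CP confirmation". The two H4 proportions are not named there.

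On analysis, Clinic/medical data begins "Descriptive statistics will be used to report participant characteristics" and assigns descriptive statistics to "Objectives 1, 2, 4, and 5, Table 4". Significance tests (Pearson's chi-squared, or Fisher's exact) "will be used to compare the extent of implementation of the best practice guidelines between regions and ethnicities", which does not cover H4.

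On size, Participants and recruitment says "There are no limits placed on the sample size, and a formal sample size calculation is not required", and that "up to 120 infants are anticipated to meet the study eligibility during the 12-month recruitment period". The number of CP cases expected among them is not given. The Discussion states that there is no control group and that infants whose families decline will not be followed.

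**The concern.** Objective 4i asks about a reduction. With no concurrent comparison, the register is the only quantitative reference, and the only stated link between the observed percentages and the register is that the former should be larger. A sample percentage falls above its own true value a large part of the time, so a cut-off placed exactly at the no-effect value separates a working Hub from an ineffective one poorly.

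At stake is how the result will be read. If the report says that H4 was met, readers will take it as an answer to objective 4i. The Discussion encourages that reading, since it says feasibility will be assessed for efficacy in reducing the age of CP diagnosis.

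**Working it through.** The plan states no power, error rate or expected number of CP cases for H4, so it has no figure of its own to reproduce. The check asks how often both H4 cut-offs would be exceeded if the Hub changed nothing.

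**Inputs**
- Rates with no effect: 17% before 6 months and 34% before 12 months (Study design and setting).
- Cut-offs: above 17% and above 34%, both required (H4).
- Number of CP cases, n: not in the document. Assumed 6 to 20. For scale, 5% to 20% of 100–120 eligible infants would be 5 to 24 cases.
- Every CP case is assumed to be followed long enough to be counted.

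**Formula.** Each CP case falls into one of three classes: diagnosed before 6 months (0.17), from 6 to under 12 months (0.34 − 0.17 = 0.17), or later (1 − 0.34 = 0.66). Let X6 and X12 be the numbers diagnosed before 6 and 12 months. Then X12 is binomial(n, 0.34). Given X12 = k, X6 is binomial(k, 0.17/0.34 = 0.5). The smallest exceeding counts are r6 = floor(0.17n) + 1 and r12 = floor(0.34n) + 1, and

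P(both) = Σ over k ≥ r12 of P(X12 = k) × P(X6 ≥ r6 | X12 = k).

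**Worked case, n = 10.** r6 = floor(1.7) + 1 = 2 and r12 = floor(3.4) + 1 = 4. P(X6 ≥ 2 | k) = 1 − (k + 1)/2^k.

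| k | P(X12 = k) | P(X6 ≥ 2 given k) | Product |
|---|---|---|---|
| 4 | 0.2320 | 0.6875 | 0.1595 |
| 5 | 0.1434 | 0.8125 | 0.1165 |
| 6 | 0.0616 | 0.8906 | 0.0548 |
| 7 | 0.0181 | 0.9375 | 0.0170 |
| 8 | 0.0035 | 0.9648 | 0.0034 |
| 9 | 0.0004 | 0.9805 | 0.0004 |

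The sum is 0.352 (k = 10 adds nothing at this precision).

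**Other case counts, same formula**

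| CP cases | Above 17% at 6 months | Above 34% at 12 months | Both |
|---|---|---|---|
| 6 | 27.1% | 33.3% | 18.9% |
| 8 | 40.6% | 54.8% | 33.9% |
| 10 | 52.7% | 45.9% | 35.2% |
| 11 | 58.1% | 54.6% | 42.7% |
| 12 | 33.4% | 38.8% | 23.4% |
| 15 | 48.2% | 40.3% | 30.1% |
| 17 | 57.1% | 54.6% | 42.0% |
| 20 | 45.0% | 54.6% | 35.7% |
| 100 | 43.6% | 45.4% | 30.5% |
| 120 | 48.0% | 51.9% | 35.8% |

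Over every whole number from 6 to 20, P(both) runs from 18.9% (n = 6) to 42.7% (n = 11). The 6-month cut-off alone is exceeded 27% to 58% of the time and the 12-month cut-off alone 33% to 55%. The movement from one n to the next is discreteness. The probability does not shrink as n grows.

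**Precision.** The smallest count above 34% with 10 cases is 4/10 = 40%, with an exact (Clopper-Pearson) 95% CI of 12% to 74%. With 20 cases it is 7/20 = 35%, CI 15% to 59%. Neither interval excludes 34%.

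**What a cleared lower limit would need, n = 10.** At 12 months, 7/10 has a lower limit of 34.8% (above 34%) and 6/10 has 26.2% (below). At 6 months, 5/10 has 18.7% (above 17%) and 4/10 has 12.2% (below). If the true 12-month rate were 60%, P(X12 ≥ 7) with n = 10 is 38%.

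**The case against.** The strongest reply is that the article contains no decision rule. H4 is a directional expectation under a secondary objective labelled limited efficacy, in a non-randomised feasibility study whose authors acknowledge the lack of a control group. Nothing says that exceeding 34% or 17% triggers progression or will be reported as efficacy. This stands. A reader might infer that H4 is formally decided on the bare percentages and that the figures above are the error rate of a planned test. The documents do not support that. The figures show how often the written expectation would be fulfilled with no effect.

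A second reply is that intervals are analysis-plan detail which a journal article may omit, and that descriptive reporting is already planned. That is right about intervals taken alone, and descriptive statistics do not exclude them. It does not reach the main point, because the cut-offs, their equality with the register rates and the descriptive analysis are all stated. The criterion is badly fixed rather than missing.

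A third reply is that requiring the lower limit to clear the register figure would turn a description into an underpowered test. The 38% above bears this out, so that condition should govern only whether the result is offered as evidence of earlier diagnosis. It should not be a criterion of the study's success.

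A reader might also infer that the small number of CP cases causes the high chance of exceeding the cut-offs. The figures at 100 and 120 cases rule that out.

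**Conclusion.** The point holds in a limited form. H4's cut-offs are the no-effect values, and with the analysis stated, an observed percentage above them does not answer objective 4i. With unchanged true rates, both would be exceeded about 19% to 43% of the time for 6 to 20 CP cases, and about 30% to 36% at 100–120. The cause is where the cut-off is placed; few cases add wide intervals.

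The range rests on an assumed case count, on register rates treated as fixed and known, and on complete follow-up. The last is doubtful. With 12 months of recruitment inside a March 2023 to September 2024 study, later entrants may not reach 12 months CGA, and CP diagnosed after the window would drop out of the denominator. That would push the observed early-diagnosis percentages up even with no effect, so the range is more likely too low than too high. The size of this was not calculated.

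The documents do not support saying that the study plans to claim efficacy from H4, or that the Hub has no effect. The feasibility objectives are untouched. The point deserves correction because objective 4i is stated and the correction is cheap.

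**What to change.** - Report the proportions diagnosed before 6 and before 12 months CGA as n/N, with the number of CP cases and exact (Clopper-Pearson) 95% CIs, beside the register figures.
- Restate H4 so that a percentage above the register figure is described as just that, and is not taken as evidence that the Hub lowers age at diagnosis unless the lower limit exceeds the register figure.
- State with the result that even a cleared limit is an uncontrolled comparison. As described, the register figures cover the catchment and are not restricted to NICU infants with newborn detectable risks. They are also given in months of age, while H4 uses CGA.

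The cost is a reworded hypothesis, a sentence or two in the analysis section and two intervals. Design, recruitment and data collection do not change. The downside is that H4 will usually be inconclusive at this size: with 10 cases, clearing both register figures takes at least 7/10 before 12 months and 5/10 before 6 months.
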